### Participants

Eligible patients have PD according to the MDS criteria [25] as confirmed by their own treating neurologists. Other inclusion criteria are (1) reduced intelligibility bothering daily communication according to the patient and/or informal caregiver(s), (2) a desire to improve their speech, and (3) willingness and ability to receive online treatment. Importantly, patients who do not own a device that is suitable for online treatment can still participate in the study, because in those cases, we will provide them with a loan device. The exclusion criteria are (1) recently received (< 1 year) speech therapy, (2) voice or speech problems due to other causes, (3) communication difficulties based on language problems without predominantly reduced intelligibility, and (4) (technical) inability to receive online treatment. Patients are not excluded by disease stage or the severity of their speech complaint, because we aim to study the effectiveness of the intervention irrespective of dysarthria severity.

The drop-out criteria are (1) withdrawal from consent and (2) health problems of such severity that conducting assessments is not possible. When willing and available, a primary informal caregiver of each patient can participate in the study by completing two questionnaires about speech and caregiver burden. Inclusion will take place over a period of 25 months, starting on March 1, 2019, and ending on March 31, 2021. Informed consent of both patient and caregiver (when applicable) is obtained by the researcher before the baseline assessment.

### Intervention

The PERSPECTIVE treatment approach combines three elements: (1) personalized treatment, (2) consistent use of a feedback app for smartphone or tablet that delivers real-time visual feedback (the Voice Trainer app), and (3) treatment delivery in the patient’s home using telerehabilitation.

#### Personalized treatment

Based on the Guidelines for Speech-Language Therapy in Parkinson’s Disease [26] and Pitch Limiting Voice treatment protocol [20], the intervention consists of 12–16 sessions (30–60 min each) in up to 8 weeks, with a maximum of three times a week and daily home exercise. The first treatment session includes an extensive assessment of the patient’s personal conversational goal [27, 28], taking into account personal circumstances and (social) environment. The caregiver is also explicitly involved and, when necessary, instructed on how to help or support the patient in doing exercises or providing trained cues. The technique to improve intelligibility will be personalized, based on the patient’s individual treatment goal. This treatment paradigm makes the treatment suitable for patients with mild to advanced hypokinetic dysarthria and has been successfully implemented in the Dutch ParkinsonNet for over a decade.

#### Support by feedback app

People with PD are highly dependent on feedback to improve motor control [29]. We therefore developed a dedicated app that provides real-time visual feedback about speech loudness and pitch: the Voice Trainer app [19]. The app supports patients and therapists to correctly practice and maintain voice loudness and pitch, during exercises as well as during conversation. As such, it supports patients in self-management and treatment compliance beyond the therapy sessions. The feasibility of the app has been confirmed by patients, caregivers, and speech therapists [30], and the use of the app has been integrated into the recently updated Guidelines for Speech-Language Therapy in Parkinson’s Disease [31].

#### Highly experienced therapists who deliver online treatment

The intervention will be delivered by highly experienced speech-language therapists who participate in the Dutch national ParkinsonNet, who have all received a dedicated 3-day training program in treating PD patients according to evidence-based guidelines, and who all treat a high caseload in their daily practice which further increases their treatment quality [22, 23]. Delivery of the online treatment will be done using a reliable, certified, and secured online platform, which is easy to use without extra costs for patients (software provided by Zaurus B.V.). Speech therapy itself will be reimbursed by the Dutch healthcare insurance, but every participating therapist is offered a small fee of €50 per patient to compensate for the extra time they spend on training and coaching (see next paragraph), thereby facilitating them to participate in the study.

### Training and coaching of trial therapists

Before the start of the trial, participating speech therapists follow a 2-day training in which they are informed about the study procedures and the PERSPECTIVE intervention protocol, including delivering online treatment. During the study period, speech therapists will be coached online by one of two experts to ensure that every patient receives optimal speech therapy. These experts have been responsible for the education of speech therapists in ParkinsonNet and the development of the voice trainer. Coaching of speech therapists takes place in a group video call with the coach, speech therapist, and patient during three online treatment sessions (weeks 1, 3, and 5), in which the coach provides live feedback to the speech therapist.

### Assessment procedures

Two assessors, who are kept blinded for the group allocation, will collect the data in the patient’s home. Questionnaires are completed online by the patient within 3 days after the assessor’s visit. Also at T0, patients receive an explanation on how to use the online platform and the Voice Trainer app. To use the Voice Trainer app and the online platform at the same time, patients need two devices (preferably a smartphone and a tablet or computer) (Fig. 2).

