## Methods/design

### Trial design

Here, we will perform a single-blinded randomized controlled trial comparing speech therapy to no intervention using a waiting list design. We opted for this design because this enables us to properly compare patients who have received therapy with patients who have not received therapy (yet), thereby answering our primary research question addressing the effectiveness of speech therapy in patients with PD. The control group receives deferred treatment directly after reassessment, which is a realistic waiting period in usual care. Patients will be assigned to either the experimental group or the control group in a 1:1 manner, by means of a computerized validated variable block randomization model using Castor EDC [24] with automatically generated block sizes of 4, 6, and 8. Stratification will take place for gender, speech therapist, Hoehn and Yahr stage, and age (< 46 years, 47–55 years, 56–65 years, > 66 years). To ensure blinding, allocation of the participants is made invisible for assessors in the data collection program Castor EDC. Furthermore, patients and speech therapists are instructed to refrain from discussing the treatment with the assessors. Measurements will be performed at baseline (T0) and after 8 weeks (T1). For the intervention group only, an additional follow-up measurement takes place 32 weeks after baseline (T2) (Fig. 1) to study whether the effects are retained at the long term. The T1 measurement is the primary endpoint at which we will compare the intervention group with the control group. The T2 measurement is the secondary endpoint at which we will compare the within-group differences of the intervention group after follow-up.

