### Procedure

Patients are asked to participate by highly experienced speech therapists, and we will recruit these speech therapists throughout the Netherlands, using the nationwide ParkinsonNet infrastructure [23]. ParkinsonNet is a national health care model that consists of 70 regional networks, with over 3000 health professionals with specific expertise in the treatment of PD patients [22]. Twelve speech therapists who participate in ParkinsonNet will be selected based on their caseload, who will each treat 16–20 patients, which is approximately 1 patient per month during the inclusion period.

During the first visit, speech therapists inform eligible patients about the study with a formal information letter. The speech therapists explicitly do not give any therapeutic advice to patients during this first visit, since patients can already benefit from education. To provide the patients enough time to consider participation, the research team calls the patients after 7 days to verify their willingness to participate and to check for eligibility. When a participant is willing and eligible, the baseline measurement (T0) is scheduled. One day after baseline measurement, randomization is performed by a researcher who is not involved in any of the measurements and who also subsequently informs both the therapist and patient about the group allocation. If the patient is allocated to the intervention group, treatment will start within a week. If the patient is allocated to the control group, treatment will start after the second measurement (T1), as shown in the flowchart (Fig. 1).

The intervention is delivered during a maximum period of 8 weeks. The number of sessions depends on the complexity of goals and possibilities of the patient (i.e., time and availability). Between T1 and T2 (only for the intervention group), patients will not receive speech therapy but still can use the Voice Trainer app.

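### As written, the baseline PDQ-39, a covariate in the primary ANCOVA, can be completed up to about 2 days after the patient has been told the allocation

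*Protocol article*

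**What the plan says.** Two sections of the protocol article set the timing.

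- Assessment procedures: "Questionnaires are completed online by the patient within 3 days after the" assessor's visit. The sentence is not restricted to the later assessments. The next one reads "Also at T0, patients receive an explanation on how to use the online platform and the Voice Trainer app", which uses T0 for the home visit.
- Procedure: "When a participant is willing and eligible, the baseline measurement (T0) is scheduled", then "One day after baseline measurement, randomization is performed by a researcher who is not involved in any of the measurements". The same researcher "subsequently informs both the therapist and patient about the group allocation". For the intervention arm, "If the patient is allocated to the intervention group, treatment will start within a week".

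The PDQ-39 is completed by the patient. Its summary index at 8 weeks is the primary outcome, and Table 1 schedules it at baseline as well. Under Analysis effectiveness, baseline values are covariates in the ANCOVA. Table 2 describes the trial as single-blind, with the outcome assessor as the blinded party. No section makes completed baseline questionnaires a condition for randomisation or for telling the patient the arm.

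**The concern.** ANCOVA relies on the covariate being unaffected by allocation. A baseline PDQ-39 answered after the patient knows whether treatment starts now or after a wait may carry a reaction to that news. It then acts as a post-randomisation variable, and adjusting for it moves the treatment estimate.

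The direction is open. Take a higher score to mean more problems. If waiting-list patients answer worse out of disappointment, the adjustment credits them with a worse starting point and the benefit is attenuated. If they answer better, or intervention patients answer worse, the benefit is inflated. Blinding the assessor gives no protection, because the patient supplies the answer.

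This is not a detail that the article merely leaves out. It states both time rules, and together they permit the overlap.

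**Working it through.** **1. The two windows, with the home visit as day 0**

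| Event | Day | Section |
|---|---|---|
| Home visit | 0 | Assessment procedures |
| Randomisation | 1 | Procedure |
| Patient told the arm | from 1 (exact time not given) | Procedure |
| Last day for questionnaires | 3 | Assessment procedures |
| First session, intervention arm | within a week; before day 3 not excluded | Procedure |

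Possible overlap: 3 − 1 = 2 days. This step needs no assumption beyond reading the baseline measurement as the visit.

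**2. The plan's own sample size**

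Inputs from Sample size calculation: difference 2.5, SD 5.8. The article gives no alpha or power. Two-sided 5% and 80% power reproduce its figure:

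n per arm = 2 × (1.960 + 0.842)² × 5.8² / 2.5² = 84.5, rounded up to 85, so 170 in total as stated.

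170 / 0.80 = 212.5, or 213, against the stated 215; the difference is immaterial. The timing point changes neither figure.

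**3. Illustrative size of the bias**

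Bias ≈ slope × share answering after disclosure × between-arm shift in their baseline score.

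The documents give none of these three inputs. The assumed ranges are slope 0.7 to 0.9, share 25% to 100% and shift 0.5 to 1.6 points. The top of the shift range equals the minimally important difference that the article cites. The formula takes the late share to be the same in both arms and the shift to be transient, so that it does not carry into the T1 score.

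SE of the difference = 5.8 × √(2/85) = 0.890.
Power if attenuated = Φ((2.5 − bias)/0.890 − 1.96).
Type I error if inflated = 1 − Φ(1.96 − bias/0.890) + Φ(−1.96 − bias/0.890).

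| Slope | Share | Shift | Bias (points) | % of 2.5 | Power if attenuated | Type I error if inflated |
|---|---|---|---|---|---|---|
| – | – | – | 0 | 0 | 80% | 5.0% |
| 0.7 | 25% | 0.5 | 0.09 | 4% | 77% | 5.1% |
| 0.7 | 50% | 1.0 | 0.35 | 14% | 68% | 6.8% |
| 0.9 | 50% | 1.0 | 0.45 | 18% | 64% | 8.0% |
| 0.9 | 100% | 1.6 | 1.44 | 58% | 22% | 37% |

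The last row is an extreme case: every patient answers late, and hearing the allocation alone moves the arms apart by a full minimally important difference.

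**The case against.** The strongest reply is that the Procedure section counts one day from the baseline measurement, not from the visit. Table 1 lists the PDQ-39 under baseline, so the measurement could include the online questionnaires, and randomisation would then follow their completion. That reading is possible and cannot be excluded. It is the less natural one, because Assessment procedures ties the window to the visit and uses T0 for the visit. The two sections need reconciling, but the article does not show that any baseline was completed late.

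A second reply is that the PDQ-39 asks how often problems occur across eight domains, including mobility and bodily discomfort, and that controls know treatment will follow. News of the arm might move the summary index very little. This also stands: the size is assumed, the sign is unknown, and the low end is negligible.

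A reader might infer three stronger claims that the documents do not support.

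- *Patients are unblinded too early.* Patients are never blinded in this trial. The issue is only when they learn the arm relative to the baseline questionnaire.
- *Control outcomes at T1 are contaminated in the same way.* Trial design does say "The control group receives deferred treatment directly after reassessment". However, it gives no number of days, and Procedure starts control treatment after the T1 measurement, whose primary endpoint is the PDQ-39 itself. Overlap would need both an early first session and a late questionnaire. Setting such T1 values to missing would remove data from the control arm only and create differential missingness.
- *The primary estimate is biased by a known amount.* No document supplies the slope, the late share or the shift.

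**Conclusion.** The point holds as a badly fixed timing rule. As written, a patient can complete the baseline PDQ-39 up to about 2 days after learning the allocation, and that value enters the primary ANCOVA. Whether this occurred, and in which direction it would act, cannot be told from the article. Under the stated assumptions the bias lies between about 0.1 and 1.4 PDQ-39 points, or 4% to 58% of the planned effect, with the upper end extreme. The conclusion rests on reading the baseline measurement as the home visit. If the questionnaires were in fact required before randomisation, one sentence saying so closes the matter. If recorded completion times show no late baselines, it closes as well.

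**What to change.** 1. **Reconcile Procedure and Assessment procedures.** State that all baseline questionnaires, including the PDQ-39, must be submitted before randomisation and before the patient is told the arm. In a trial still recruiting, this would delay randomisation by at most about 2 days for some patients.

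2. **Use the data already collected.** Trial status says inclusion was finalised in March 2021, so the rule can no longer protect any baseline here. Report by arm how many baseline PDQ-39s were completed after disclosure. First check that the times are patient completion times. Assessment procedures says only that completion is online, while Data management has assessors entering the data in Castor, so an audit-trail time could be an entry time.

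3. **Pre-specify a sensitivity analysis before results are seen**, keeping all randomised patients. Either set late baseline values to missing and impute them from pre-randomisation data, or omit the baseline PDQ-39 adjustment. Other questionnaires share the 3-day window, so only those completed before disclosure should inform the imputation. A change-from-baseline analysis is no substitute, because it applies a slope of 1 to the same affected value.

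4. **For T1**, at most report how many control questionnaires were completed after deferred treatment began.

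The cost is modest extra analysis work and some precision in the sensitivity analysis only. Imputation costs little if few values are late. Omitting the adjustment costs more: if the baseline–T1 correlation equals the assumed slope, the standard error grows by a factor of 1/√(1 − 0.7²) = 1.40 to 1/√(1 − 0.9²) = 2.29. The sample size does not change.

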**Fig. 2 Fig2:**
[figure not shown]
Setup of using the Voice Trainer app and online platform. **A** Smartphone with voice trainer is correctly placed in a smartphone holder. **B** Smartphone is aimed at the camera of the second device (computer or tablet). **C** Voice trainer is visible for both patient and speech therapist on their computer screen

### Outcome measures

#### Primary outcome measure

Our primary endpoint is quality of life using the summary index score of the Parkinson’s Disease Questionnaire (PDQ-39) at 8 weeks follow-up (T1) [32, 33]. We have chosen the PDQ-39 as the primary outcome, because a positive impact of speech therapy on the lives of patients with PD is our highest goal. The PDQ-39 is a disease-specific measure of subjective health status and contains 39 questions, divided over eight important areas of health status: mobility, activities of daily living, emotional well-being, stigma, social support, cognitions, communication, and bodily discomfort. Patients indicate for every question how often they experience problems on a 5-point scale (never, seldom, sometimes, often, or always). A profile of scores can be calculated, indicating the impact of PD in the eight dimensions. The summary index score (SI) is calculated from the eight profile scores and provides an indication of the global impact of PD on health status. Studies evaluating the PDQ-39 show high levels of validity and reliability [32, 34]. The PDQ-39 is known as the most widely used PD-specific health-related quality of life questionnaire [35].

#### Secondary outcome measures

All secondary outcome measures are listed in Table 1 and include evaluation of speech and voice quality, voice handicap, speech intelligibility, severity of voice and speech complaints, mood and anxiety, health-related quality of life, and swallowing speed (the latter because of the possible impact of speech improvement on swallowing efficiency) [49]. Outcome measures at the caregiver level are caregiver burden, and caregiver reported severity of voice and speech complaints.

**Table 1 Tab1:** Schedule of measurements and outcome measures

Background variable	Instrument	Baseline	8 weeks	32 weeks^**1**^
Age, gender, disease duration, presence of advanced therapy	n.a.	√		
Cognitive functioning	Mini-Mental State Examination (MMSE) [36]	√		
	Category fluency task (animals) [37]	√		
Disease severity	Hoehn and Yahr stage [38]	√	√	√
	Total score on Movement Disorder Society - Unified Parkinson Disease Rating Scale (MDS-UPDRS) [39]	√	√	√
**Outcome measure**	**Instrument**			
Health-related quality of life	Parkinson’s Disease Questionnaire (PDQ-39) [32–34]	√	√	√
	EuroQol-5D (EQ-5D) [40]	√	√	√
Speech quality	Radboud Dysarthria Assessment (RDA) [41]	√	√	√
Voice quality	Acoustic Voice Quality Index (AVQI) [42]	√	√	√
Voice handicap	Voice Handicap Index (VHI) [43]	√	√	√
Severity of voice and speech complaints, reported by patient	Radboud Oral Motor inventory for Parkinson’s disease (ROMP) [44]	√	√	√
Severity of voice and speech complaints, reported by caregiver	Radboud Oral Motor inventory for Parkinson’s disease (ROMP), adapted to caregiver	√	√	√
Speech intelligibility	Dutch intelligibility test – sentence level (NSVO-Z) [45]	√	√	√
Caregiver burden	Zarit caregiver Burden Interview Short Form (ZBI-12) [46]	√	√	√
Mood and anxiety	Hospital Anxiety and Depression Scale (HADS) [47]	√	√	√
Swallowing	Maximum swallowing speed (timed test) [48]	√	√	√

^1^T2 will only be performed in patients who were allocated to the intervention group

#### Background variables

Demographic data are collected at baseline and consist of age, gender, disease duration, and possible presence of advanced therapy, e.g., deep brain stimulation, subcutaneous apomorphine infusion, or levodopa-carbidopa intestinal gel. Patient’s disease severity will be measured with the Movement Disorder Society – Unified Parkinson Disease Rating Scale (MDS-UPDRS [39];), including the Hoehn and Yahr scale. The Mini-Mental State Examination (MMSE [36];) and a category fluency task are used to assess general cognitive functioning. Demographic data, disease severity, and cognitive functioning will be used to describe the study population.

### Sample size calculation

Based on a trial on the effectiveness of multidisciplinary care [50], we have calculated the sample size on our primary outcome with a conservative estimated PDQ-39 total score improvement of 2.5 points (SD = 5.8) in the intervention group, and no difference in controls. This estimated improvement exceeds the minimally important difference of 1.6 points [33]. A sample of 170 patients would be needed to show this expected difference. Allowing for 20% drop-out, we will include 215 patients.

### Statistical analysis

#### Descriptive statistics

Means, standard deviations, and frequencies will be used to describe the outcome, background, and baseline variables.

#### Analysis effectiveness

Based on our hypothesis and design, two comparisons will be made: (1) the between-group differences at the primary endpoint (T1) and (2) the within-group differences in the experimental group after 24 weeks of follow-up (T1 versus T2). Statistical analyses will be performed based on the intention-to-treat principle. Analysis of covariance will be used with each of the outcomes as a dependent variable and group allocation as a fixed variable. Baseline values, age at baseline, Hoehn and Yahr stage, and disease duration will serve as covariates. We will also perform a process analysis and a planned post hoc analysis to identify which factors predict a successful outcome.

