## Discussion

The PERSPECTIVE study is a large, well-designed, randomized controlled trial evaluating the effectiveness of speech therapy in persons living with PD. Particular strengths of our study include the randomized and controlled design, the personalized treatment approach, the inclusion of PD patients irrespective of the disease stage, the long-term follow-up, the adequate power, and the choice for a patient-relevant primary endpoint.

We believe that the ultimate goal of any treatment for persons with PD is a relevant improvement of their quality of life. Intelligible speech is certainly thought to contribute to this, because we expect that patients are better able to handle communicative and social situations when their speech is more intelligible, which in turn will likely have a positive impact on quality of life. Obviously, there are many other factors that could affect the quality of life, like mobility, emotional well-being, or bodily discomfort. Taken together, choosing the quality of life as our primary endpoint is highly relevant for patients but also challenging at the same time, because it is only partially dependent on intelligibility. That is why we based our power calculation on finding a small, but clinically relevant improvement of quality of life after speech therapy.

The PERSPECTIVE study is a complex study, because we conduct our research in daily practice, with patients receiving the treatment within their own homes, instead of in a fully controlled situation within a hospital environment. While challenging, this remote home-based approach allows us to gain a realistic and generalizable view on the effectiveness of speech therapy in PD. We will discuss some of these challenges here.

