The first challenge is that therapy is delivered by multiple speech therapists, which may be accompanied by inter-individual differences in treatment quality, which may in turn impact the results of the trial. In order to minimize this treatment variability, all speech therapists are being coached by an expert speech therapist for every single patient that is allocated to the experimental group. Moreover, all participating therapists are part of a professional network, which includes a thorough 3-day Parkinson-specific training course according to the latest guidelines prior to participation, as well as ascertainment of a high caseload in daily practice. In this way, we have taken specific measures that help to ascertain a delivery of high-quality treatment for every patient participating in the trial. An advantage is that we may be able to extrapolate the trial findings more readily to everyday clinical practice, as compared to studies that were performed on the more carefully controlled in clinic situations.

The second challenge is that we aim to include patients in all disease stages and with all grades of dysarthria severity, because we want to understand the effectiveness of the intervention for the full severity range, like it is presented in day-to-day clinical practice [51]. This leads to a heterogeneous study population, and therefore to more variation in the data, which could impact the power of our analysis. However, although the size of treatment results will differ between patients, we anticipate to show that dedicated speech therapy can make a difference for every PD patient with speech problems.

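### The primary ANCOVA leaves out two stratification factors, gender and speech therapist, and has no term for therapist clustering in the treated arm; precision is lost, or the standard error is too small if the treatment effect varies by therapist

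*Protocol article*

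**What the plan says.** The Trial design section of the protocol article says: "Stratification will take place for gender, speech therapist, Hoehn and Yahr stage, and age". Allocation is equal: "Patients will be assigned to either the experimental group or the control group in a 1:1 manner".

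The Analysis effectiveness section specifies an analysis of covariance with group as a fixed factor and then lists the adjustment: "Baseline values, age at baseline, Hoehn and Yahr stage, and disease duration will serve as covariates". Two of the four stratifiers (age, Hoehn and Yahr stage) are carried over and two (therapist, gender) are not. Disease duration, which is not a stratifier, is added.

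The Procedure section plans twelve therapists with 16–20 patients each, and starts treatment of controls only after the 8-week measurement (T1). The Discussion concedes that delivery by several therapists may bring "inter-individual differences in treatment quality, which may in turn impact the results of the trial". It answers with training and with expert coaching for every experimental patient, not with an analysis term.

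The Sample size calculation assumes a "conservative estimated PDQ-39 total score improvement of 2.5 points (SD = 5.8) in the intervention group, and no difference in controls" and concludes: "A sample of 170 patients would be needed to show this expected difference". It then adds: "Allowing for 20% drop-out, we will include 215 patients". It mentions no allowance for therapist. The Discussion lists "the long-term follow-up, the adequate power" among the strengths of the study.

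**The concern.** The article states the primary model and its covariates explicitly, so this is a mismatch between stated design and stated analysis, not a detail left to an unseen analysis plan.

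Two separate things are at stake, and they act in different directions:

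- **Therapist and gender as prognostic factors.** If they shift outcomes equally in both arms, stratifying on them and then leaving them out of the model puts variation in the residual that the design has partly balanced. The standard error is then too large or about right, and some power is given up.
- **Therapist as the source of treatment.** At T1 only intervention patients have been treated. If some therapists achieve more than others, outcomes of treated patients who share a therapist are correlated, while controls have no such correlation. This is a partially nested design. A model that treats all patients as independent then gives a confidence interval that is too narrow.

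**Working it through.** **1. The plan's own figure.** Inputs from the Sample size calculation: difference 2.5, SD 5.8. Alpha and power are not stated; two-sided 5% and 80% are assumed.

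- n per arm = 2 × (1.960 + 0.842)² × 5.8² / 2.5² = 84.5, rounded up to 85, so 170 in total. This matches the stated number. One-sided 5% with 80% power gives 134, one-sided with 90% gives 186, and two-sided with 90% gives 228.
- Drop-out: 170 / 0.8 = 212.5, so 213, against 215 stated. The two agree closely.
- SE = 5.8 × √(2/85) = 0.890. Power = Φ(2.5/0.890 − 1.960) = 80.2%.

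The 170 is therefore correct for independent patients.

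**2. Treatment effect varies by therapist (clustering in the treated arm only).** Evaluable treated patients per therapist: m = 85/12 = 7.08. The ICC is an assumption, because the document gives none.

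- Design effect in the treated arm: DE = 1 + (m − 1) × ICC
- Ratio of true to planned SE: √((DE + 1)/2)
- Actual type I error of the planned test: 2 × (1 − Φ(1.960/ratio))
- Power of a test with the correct SE: Φ(2.5/(0.890 × ratio) − 1.960)

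Example for ICC 0.05: DE = 1 + 6.08 × 0.05 = 1.304; ratio = √(2.304/2) = 1.073; type I error = 2 × (1 − Φ(1.826)) = 6.8%; power = Φ(2.5/0.955 − 1.960) = 74.5%.

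| ICC | DE | SE ratio | Type I error | Power | N for 80% (with 20% drop-out) |
|---|---|---|---|---|---|
| 0 | 1.000 | 1.000 | 5.0% | 80.2% | 170 (213) |
| 0.01 | 1.061 | 1.015 | 5.4% | 79.1% | 176 (220) |
| 0.02 | 1.122 | 1.030 | 5.7% | 77.9% | 180 (225) |
| 0.05 | 1.304 | 1.073 | 6.8% | 74.5% | 200 (250) |
| 0.10 | 1.608 | 1.142 | 8.6% | 69.2% | 248 (310) |

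The last column keeps twelve therapists, so m grows with N. The normal approximation ignores the limited degrees of freedom from twelve therapists.

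**3. Simulation check** (2,500 trials per scenario, N = 170, 12 therapists; the mix of gender, stage and age is illustrative). Ranges cover stratification by therapist and by all four factors crossed. Monte Carlo error is about ±0.9 points near 5% and ±1.6 points near 80%.

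| Treated-arm ICC | Type I error, planned covariates | Type I error, therapist and gender added as fixed factors |
|---|---|---|
| 0.02 | 5.2% | 5.1–5.4% |
| 0.05 | 7.0–7.7% | 7.3–7.5% |
| 0.10 | 8.8–9.7% | 9.3–9.4% |

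Fixed factors leave the error essentially unchanged.

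**4. Therapist and gender prognostic only.**

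- Therapist ICC 0.10, gender effect 0.3 SD, randomisation balanced by therapist: mean model SE about 0.89 against a true 0.84–0.85 without adjustment; type I error 4.0%; power 80.5% against 84.4% with adjustment.
- The same effects with all four factors crossed: type I error 4.8%; power 79.5% against 81.8%.
- Weaker effects (ICC 0.05, gender 0.2 SD): 80.9% against 82.0% when balanced by therapist, but 79.8% against 78.5% with crossed strata. The gain is not guaranteed.

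**The case against.** The strongest reply has four parts.

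- **The size rests on an ICC that the document does not give, and there are reasons to expect a low one.** The Discussion says that quality of life depends only partly on intelligibility, and an expert coaches the therapist for every treated patient in weeks 1, 3 and 5. This stands: up to an ICC of 0.02 the effect is minor. Coaching may reduce therapist variation, but it does not account for what remains.
- **The inflated type I error needs a particular null: an average effect of zero with effects that differ between therapists.** If therapy changed nothing for anyone, delivery would create no correlation. This also stands. The interval is still too narrow when there is a real average effect; by the same formula, coverage is 94.3% / 93.2% / 91.4% at ICC 0.02 / 0.05 / 0.10.
- **The strata are sparse.** Twelve therapists × 2 genders × 4 age bands is 96 cells before Hoehn and Yahr stage, for 215 patients, so little balance by therapist may be achieved. This weakens the precision argument, as the crossed-strata results show, but not the clustering argument.
- **This is a condensed article, and a separate analysis plan may handle clustering.** Silence on an ICC alone would be no finding. The explicit covariate list, set against the explicit stratification, is.

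A reader might go further and infer that the stated standard errors and power are wrong. The documents do not support that. They state no standard error and no numerical power, and 170 reproduces exactly. Nor does leaving out gender make intervals too narrow; it costs at most some precision. Chance imbalance between therapists is not an error either, since the standard error already covers it.

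**Conclusion.** The point holds in conditional form. The stated primary model does not reflect two of the four stratification factors, and nothing in it represents therapist variation in the treated arm, which the article itself thinks possible.

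The consequence depends on the kind of variation. Purely prognostic effects leave the analysis valid or mildly conservative, at a cost of up to about four points of power in the scenarios tried. Variation in the treatment effect understates the standard error, by a factor of 1.03 to 1.14 over the assumed ICC range of 0.02 to 0.10; this is material from about 0.05.

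The figures assume two-sided 5%, 80% power, 85 evaluable patients per arm spread evenly over twelve therapists, SD 5.8 as the residual SD, and therapist correlation in the treated arm only. The mismatch between design and model is certain; its size is not. It should be corrected, but it does not invalidate the trial.

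**What to change.** In the Analysis effectiveness section:

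1. Add gender and speech therapist to the covariates of the primary T1 model, so that it reflects the stratification, or give a reason for leaving them out.
2. Add a therapist effect in the treated arm (a partially nested model or a random therapist-by-treatment term) with a small-sample degrees-of-freedom correction, as the primary analysis or as a prespecified sensitivity analysis. Step 1 alone can recover precision but does not correct the clustering.
3. State that the claim of adequate power assumes no therapist clustering, and give power over a range of ICCs such as the one above.

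Both variables are already recorded for randomisation, so no new data are needed. The price is a possibly wider confidence interval, a few degrees of freedom, and a variance component that twelve therapists with about seven evaluable treated patients each will estimate imprecisely. The plan should therefore also say what is done if that component is estimated at zero or the model does not converge. Recruitment has ended, so step 3 changes how the result is read and not the sample size.
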